### Recruitment, consent and randomization

2.2

In order to be eligible to participate, patients must meet the following criteria: (1) diagnosed with PD according to the UK-brain banking criteria [43]; (2) ≥ eighteen years of age; (3) ≥ four different medications daily; (4) ≥ four medication intake moments daily; (5) expressing motor and non-motor symptoms; (6) living (semi)-independent in the region of Enschede, Almelo, Hengelo or Zwolle; (7) be able to read and write the Dutch language. Exclusion criteria are: (1) being unable to administer their own medication, e.g. when requiring assistance from medical home care. PD patients receiving help from personal or family caregivers were not excluded based on this criterium; (2) having received a medication review within a year prior to the study; (3) having received a Deep Brain Stimulator, continuous duodopa gastro-intestinal gel therapy or continuous apomorphine therapy within a year before the study or willing to receive this within three months.

As soon as informed consent is obtained by the investigator and baseline measurements are performed, patients will be randomly assigned in a 1:1 ratio with a blinded blocked randomization with block sizes of four and eight. Inclusion is definite when patients in the intervention group complete the baseline measurements and receive an SMR, while patients in the control group only need to complete baseline measurements.

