### Intervention

2.3

Community pharmacists will perform the SMR at the start of the study within the intervention group, while the control group will receive usual care and will not have a medication review during the next six months. All pharmacists are offered an accredited training regarding PD and drug treatment, the study protocol and the execution of an SMR beforehand. The latter is based on the Dutch Systematic Tool to Reduce Inappropriate Prescribing (STRIP)-method [44], a standardized tool for pharmacists for executing SMRs in Dutch patients. This method highly emphasizes the importance of involving the patient as a full partner in evaluating all medicines on drug-drug interactions, adverse reactions and problems with dosing or drug use. Possible barriers to adherence and non-adherent behavior are identified by asking questions in a non-judgmental way [45,46]. Possible interventions will be suggested, taking the patient's preferences, views and beliefs about their medicines in full account.

To ensure continuity of care and to facilitate collaboration between health care providers, clear documentation is required, for which a protocol is chosen based on the action plan for medication assessment of the Multidisciplinary guideline Polypharmacy in the Elderly and the abovementioned STRIP-method [44] (see Appendix). The protocol foresees the possibility of consulting a General Practitioner, neurologist and other specialists if necessary. Any adjustments in the medication regime will be communicated and explained to the patient.

After the review has been performed, all pharmacists record their proposed medication modifications or interventions, recommendations and possible other findings. This is sent to the collaborating health care providers. Together with the patient, the applied interventions will be evaluated within 4 months either by telephone or face-to-face.

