#### Secondary outcomes

2.4.2

Secondary objectives include activities in daily life and physical disability (AMC Linear Disability Scale (ALDS) [52]; non-motor symptoms (Non-Motor Symptoms Questionnaire (NMS-Quest) [53,54] and health status (EuroQOL-5 Dimensions-5 Levels (EQ-5D-5L, including Visual Analogue Scale (VAS) [55,56]. By using the index-based values of the EQ-5D-5L, quality adjusted life years (QALY) can be calculated, necessary for assessing the cost-effectiveness of an intervention [55]. Costs need to be taken into account to calculate these QALYs and to compare the cost-effectiveness of the SMR with other interventions in patients with PD. Costs incurred during this study are costs of medication, hospitalization, outpatient visits and home care, and the costs associated with the SMR. To assess the effects on QoL for personal or home caregivers, the PDQ-Carer questionnaire will be used [57].

All SMR forms will be collected to analyze modifications in medication regime and recommendations given to patients. This will be used descriptively.

Semi-structured, face-to-face interviews with community pharmacists will be conducted after at least one SMR has been performed by the pharmacist, to obtain insight in probable bottlenecks in the process of performing medication reviews. Interviewing will take place till data saturation has been reached.

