### Data analysis

2.7

Between-group differences in categorical variables will be analyzed using a Chi-square test or Fisher's exact test, as appropriate, while continuous variables will be analyzed using t-tests or a Mann-Whitney test, as appropriate. Continuous data will be presented as means with standard deviations (SD) in case of normal distributions or as medians with interquartile ranges (IQR) in non-normal distributions. For all continuous variables, a repeated measurement analysis will be performed to deal with possible missing data. According to the PDQ-39 manual, missing data will be imputed using Expectation Maximization [58].

The approach of a modified intention-to-treat analysis will be used, which essentially means that to include patients in this study, patients in the intervention group need to receive an SMR after baseline questionnaires are completed, and patients in the control group need to complete baseline questionnaires after randomization.

Secondly, a sensitivity analysis will be performed to measure the effects of an SMR in patients in whom at least one medication regimen change was implemented or to whom at least one recommendation has been given.

Data will be analyzed using SPSS version 24. P-values ≤ 0.05 are regarded as statistically significant. Data concerning the semi-structured interviews will be imported in and analyzed with Atlas Ti version 8.

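### The planned sensitivity analysis seeks an SMR effect in patients selected by a result of the SMR, a status that cannot be identified in controls

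*Protocol article*

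**What the plan says.** Section 2.7 (Data analysis) first defines a modified intention-to-treat set, for which "patients in the intervention group need to receive an SMR after baseline questionnaires are completed", while controls need only complete baseline questionnaires. It continues: "Secondly, a sensitivity analysis will be performed", with the aim "to measure the effects of an SMR in patients in whom at least one medication regimen change was implemented". The criterion is then widened by a second limb: "or to whom at least one recommendation has been given". Either condition is enough to qualify.

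Three other places bear on this:

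- **Section 2.2 (Recruitment, consent and randomization).** After consent and baseline measurement, "patients will be randomly assigned in a 1:1 ratio".
- **Section 2.3 (Intervention).** "After the review has been performed, all pharmacists record their proposed medication modifications or interventions", so the facts that define the subset arise after the review and therefore after randomisation. In the other arm, "the control group will receive usual care and will not have a medication review during the next six months".
- **Section 2.4.2 (Secondary outcomes).** The SMR forms are collected to analyse regimen modifications and recommendations, and "This will be used descriptively".

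For this second analysis the article states no comparator, no matched control subset and no adjustment. It does not call the analysis exploratory.

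**The concern.** Randomisation makes the two arms comparable as wholes. It does not make part of one arm comparable with the whole of the other. Whether a review ends in a change or a recommendation depends on the patient: the drug-related problems found, adherence, the complexity of the regimen and willingness to accept a change.

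The article itself ties these features to the primary outcome. The Abstract and Introduction link complicated regimens, poor adherence and drug-related problems to reduced quality of life. Selected and unselected patients would therefore be expected to differ on PDQ-39 even without a review.

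The label is also wrong. A sensitivity analysis varies an assumption of the main analysis to see whether the conclusion holds. This one changes the population in one arm only and tests no such assumption. The result is likely to be read as the effect in patients for whom the review led to something, although part of it may be selection.

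**Working it through.** The plan gives no figure for this analysis, so there is none to reproduce. The check has two parts.

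**1. Can the criterion be applied in both arms?**

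| Element | SMR arm | Control arm |
|---|---|---|
| Review held | Yes, at the start of the study (2.3) | No, not for six months (2.3) |
| Recommendation from an SMR | Recorded after the review (2.3) | Cannot exist |
| Regimen change | Recorded and followed up after the review (2.3) | May occur under usual care, but is not equivalent, and 2.7 does not plan to select on it |

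The control patients who would have qualified exist but cannot be observed.

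**2. How large could the bias be if the comparator is all controls?**

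Let q be the share of SMR patients selected. Let m1 and m0 be the mean untreated PDQ-39 of patients who would and would not be selected, d = m1 − m0, and T the true effect in the selected. Assume that the two arms as analysed are otherwise comparable.

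- Selected SMR patients: m1 + T
- All controls: q·m1 + (1−q)·m0
- Difference: T + (1−q)·d

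The bias is therefore (1−q)·d. Neither q nor d is in the documents. Assumed values:

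| q | d (points) | Bias (1−q)·d |
|---|---|---|
| 0.7 | 10 | 0.3 × 10 = 3.0 |
| 0.8 | 8 | 0.2 × 8 = 1.6 |
| 0.9 | 5 | 0.1 × 5 = 0.5 |

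The yardsticks in 2.5 are a minimally important difference of 1.6 points and an expected effect of 4. On the stated SD of 15, a d of 5 to 10 points is 5/15 = 0.33 to 10/15 = 0.67 SD.

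*Second model.* Take a true effect of zero, SD 15 and 99 per arm (2.5). Patients are selected when a normal latent proneness to a change or recommendation exceeds a cut-off c. Its correlation with PDQ-39 is r, which is assumed. The spurious difference is 15·r·φ(c)/q, with c set so that a share q is selected. Rejection rates come from 4,000 simulated trials tested at a nominal 5%.

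| q | r = 0.2: bias | r = 0.2: rejection | r = 0.3: bias | r = 0.3: rejection |
|---|---|---|---|---|
| 0.5 | 2.4 | 15.5% | 3.6 | 28.4% |
| 0.7 | 1.5 | 9.8% | 2.2 | 15.9% |
| 0.8 | 1.0 | 7.8% | 1.6 | 11.0% |
| 0.9 | 0.6 | 5.7% | 0.9 | 6.5% |
| 0.95 | 0.3 | 5.4% | 0.5 | 6.5% |

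The bias is zero only if r = 0 or q = 1. A bias of 3.0 at q = 0.7 would need r of about 0.4.

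*Direction.* A higher PDQ-39 score means lower quality of life (2.4.1). If the selected patients are worse off (d > 0), a benefit is masked. If they would have done better anyway (d < 0), a benefit is exaggerated or created.

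**The case against.** - **No comparator or model is stated, and a condensed article may leave these to the analysis plan.** This stands as far as it goes: the bias figures depend on the subset-versus-all-controls reading. It does not rescue the analysis, because the article fixes the population and the aim, and no randomised counterpart can be observed. A before-after change within the subset would carry time trends and regression to the mean.
- **The criterion is wide.** Participants take at least four medicines at four or more daily intake moments (2.2), and every medicine is reviewed (2.3). A single recommendation is enough, so q may be close to 1. This is plausible, although the documents give no share. The bias would then be small, and the result would nearly repeat the main analysis.
- **Baseline adjustment would help.** PDQ-39 is measured before randomisation, and 2.7 plans a repeated measurement analysis for continuous variables. If that analysis uses change or adjusts for baseline, stable differences largely drop out and d becomes a difference in course, for which 5 to 10 points is much less plausible. This stands, so the 0.5 to 3.0 range is for an unadjusted comparison. Adjustment cannot remove unmeasured differences such as willingness to change.
- **It is only a supporting analysis.** This also stands. A reader might infer that the trial's main result is compromised, but the documents do not support that: this subset plays no part in the primary comparison. That the main set already requires receipt of an SMR in one arm only is a separate matter.

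**Conclusion.** The point holds for the analysis as described. It selects on a result of the intervention that is observable in one arm only, so it cannot deliver the SMR effect that it sets out to measure, and it is not a sensitivity analysis of the primary result.

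The size is uncertain. On the likely reading, unadjusted, the bias is about 0.5 to 3.0 points in either direction for assumed q of 0.7 to 0.9 and d of 5 to 10. The upper part of that range exceeds the 1.6-point minimally important difference. With baseline adjustment it would be smaller, and with q near 1 it would be close to zero.

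A reader might infer that the bias could equal the effect sought. These figures do not show that: the largest value in the range is 3.0 points against an expected effect of 4, and it needs assumptions at the unfavourable end. Nor can it be said that the reported estimate will certainly be confounded by a given amount, since comparator, adjustment, q and d are all unstated. This is a correction worth making to a supporting analysis.

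**What to change.** **Change.** In 2.7, stop presenting this as a sensitivity analysis or as an effect of the SMR. Report patients with a change or recommendation as a description within the SMR arm: how many there are, their baseline characteristics and their PDQ-39 course, without a p-value or effect claim. This agrees with the descriptive use of the SMR forms in 2.4.2. It costs only wording.

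**Optional supplement, if an effect estimate is wanted.** Add a complier-average causal effect analysis in all randomised patients with follow-up. Use two-stage regression with randomised arm as instrument, a change or recommendation as exposure (zero in controls) and adjustment for baseline PDQ-39. State with it that:

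- it assumes that an SMR without a change or recommendation has no effect. This may fail, because the Discussion concedes that the lack of blinding may raise awareness of medication use, and the SMR itself explores barriers to adherence (2.3);
- it needs follow-up of randomised patients who did not receive an SMR. The inclusion rule in 2.2 may not secure this, so it can cost more than one extra regression;
- before covariate adjustment it is roughly the arm difference divided by q. An arm difference of 4 points would become 4/0.7 = 5.7 or 4/0.9 = 4.4, with a confidence interval wider by about 1/0.7 = 1.43 or 1/0.9 = 1.11. If q is near 1, it adds little.

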## Discussion

3

The complexity of PD easily leads to compliance issues and DRPs. This calls for a structured strategy to monitor pharmacological care. Additionally, as no ‘one size fits all’ principle can be applied to treat PD, a patient-centered approach is required. In this trial, the impact of an SMR on QoL in PD patients will be investigated.

Although previous research in different settings of care assumes a positive effect of an SMR on health outcomes such as QoL and cost-effectiveness, contradictory results are found. Willeboordse et al. (2017) found no effect of a medication review concerning QoL in 518 geriatric patients and the chronic use of ≥1 prescribed drug [59]. One explanation might be the non-complexity of the selected patient group. More specific high risk patient groups should be targeted, for whom SMRs might be of added value [21,35,36,60]. A recent study by Marvin et al. (2018) showed that in an acute in-hospital setting, a combination of age, problematic polypharmacy and the presence of DRPs were the most important criteria to identify these high risk patients [37].

An SMR appears to be time consuming and labor intensive [14,35,61]. In the Netherlands, community pharmacists should conduct SMRs as part of standard care with only a low contractual remuneration by the covering health insurance companies [60]. The prevention of DRPs and safety of medicines have become an important discipline in health policy as well as in medical and pharmaceutical care. PD patients seem to be a logical target, given their complex medication regimen. This suggests that an SMR in these patients might be of high value. Nevertheless, not much is known yet about the effect of SMRs on clinical endpoints like QoL in this patient group. A pilot from Stuijt et al. (2017) found that multifaceted pharmacist-led interventions improved medication adherence in 23 PD patients, with a significant positive effect on QoL. The effect of separate interventions could not be assessed, although the best improvement of motor symptoms resulted from the addition of the SMR, performed by one co-located pharmacist in an outpatient PD clinic [62].

A strength in our study is that since patients are included together with their own community pharmacists, our results may be more generalizable. The training that community pharmacists are offered in order to standardize pharmaceutical care, might furthermore positively affect the quality of an SMR, as informed pharmacists might understand more about PD, its symptoms, complications and treatment, and how to respond to a patient's demand.

Considering the experience of previous studies in a similar setting, we choose to include PD patients with not only polypharmacy, but at the same time the need to take medicines at least 4 times daily, which is an extra factor contributing to complex medication regimens [24]. This may further select the high-risk patient group in need for optimizing therapy by an SMR.

In addition, since a cost-effectiveness analysis will be part of our study, the effects of an SMR in PD patients might eventually provide more evidence for further translation into practice.

Nevertheless, potential limitations according to the study protocol should be discussed. First, although justified by the nature of the intervention, randomization is not blinded. This might lead to increased awareness of medication use in the intervention group patients beforehand, whereby the effect of the intervention may be influenced. Also, due to the selection of patients, compliance in clinical trials often is substantially higher compared to actual practice [29].

Finally, with regard to a patient's HY-stage, the most accurate assessment would be physical evaluation. However, since patients are recruited by phone, this physical test would place an additional burden on the patient and their possible caregiver and might result in lower recruitment rates. Therefore, the HY-stage will be distracted from the electronic patient file in this research and in case of uncertainty verified by the treating neurologist.

Our trial has the support of the Royal Dutch Society for Pharmacy, which may help to promote the implementation of pharmaceutical care in this setting if the current study proves the effectiveness of an SMR in patients with PD.

## Ethics approval and consent to participate

Ethical approval for this study was provided by the Medical Ethical Review Board Twente, the Netherlands (reference number NL48661.044.14). Written informed consent will be obtained from all participants.

## Trial registration

The research protocol is registered in the Dutch clinical trial register: NTR4500.

## Consent for publication

Not applicable.
